#### Who will take informed consent? {26a}

The investigators will identify eligible participants based upon inclusion and exclusion criteria. A detailed written and oral information on the study will be provided to the patients in an understandable language (English/Odia), and the investigators will take written informed consent.

#### Additional consent provisions for collection and use of participant data and biological specimens {26b}

The written consent will include information regarding videography of the procedure of intubation and the use of relevant data for academic purposes.

### Interventions

#### Explanation for the choice of comparators {6b}

##### An explanation for the selection of the intubator

It was hypothesized that we would need to include trainees who had a good knowledge of and experience for proper laryngoscopy, so that poor vision of the glottis would not confound the time to intubation. We did not want to include personnel who were very experienced as various other subtle “learned/subconscious” maneuvers would be difficult to predict or control for. As per previous studies, 40–60 LEIs on patients or manikins were considered adequate [1, 4].

##### An explanation for the site of holding the ET

The two sites of holding the ET were selected, based on a pilot study involving video recording the procedure of intubation by 54 experienced (>3 years) anesthesiologists. The mean site of holding the tube was 21.3 cm with a standard deviation (SD) of 2.5 cm. Hence, two groups’ extremes from the mean ± 1 SD were chosen and rounded up to the nearest number, one at 19 cm (group 1) and the other at 24 cm (group 2).

#### Intervention description {11a}

##### Equipment

All emergency airway and resuscitation equipment will be available. ETCO2 enabled anesthesia machines, and SpO2 probes will be in place.

##### Personnel

1. The consultant anesthetist and trainee will position the patient and prepare for intubation.

2. The operation theater technician (not a part of the research team) will select a sealed envelope after the patient enters the theater and the WHO checklist is completed. He will then mark the endotracheal tube at the site the patient has been randomized to19 or 24 cm with a transparent sticker.

3. A trainee technician (not a part of the research team) will be positioned in a way such that the entire process is visible and will video record the procedure.

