### Eligibility criteria {10}

The participants included in the study will be:
i.Patient: Adult patients (age > 18 years) with ASA I to II functional status undergoing elective/emergency surgical procedures under general anesthesia who can understand and provide valid consent for the procedure. The exclusion criteria will be patients less than 18 years of age, American Society of Anesthesiologists (ASA) > 2 functional status, patients having Cormack Lehane (CL) grading more than 2 on direct laryngoscopy, use of airway adjuvants, and refusal to give consent for the study.ii.Intubator: Intervention (intubation) will be performed by trainee anesthesia residents who have less than 18 months of experience. As a part of the curriculum, training in the theory of airway management and mannikin intubations will ensure that all the trainees have experience of a minimum of 40 intubations on mannikins or patients. A consultant anesthetist will supervise all intubations per protocol.iii.Procedure: All procedures will be video recorded from the time patient is positioned after induction, and the laryngoscope is asked for, to after confirmation of correct tube position (this may be visual, auscultatory, or EtCO2 guided). Procedures where the trainee deviates from the methodology, improper table position, CL grade found > 2, use of a bougie, stellate, or other airway adjuncts, or take-over by the consultant (unanticipated difficult airway), will be video recorded but excluded from the analysis. This will reduce confounding the time to intubation due to poor visualization of the laryngeal inlet.

A few cases will be tried with a Go-Pro camera, hoping to ascertain data for the exact laryngoscopy view (with the understanding that the visual axis of the camera will not be identical to the LEI, and the forehead mounted camera might make the process more cumbersome for the trainee).

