#### Technique

After induction and a minimum of 3 min of administering the paralytic agent, the intubator will perform the laryngoscopy. Once the intubator declares that the CL grade is optimal (CL < 3), it will be confirmed by the faculty or senior either verbally or visually. Once declared as an “optimum laryngoscopic view,” the tube will be handed over by the technician to the intubator and prior instruction will be given to take the first attempt at the marked point, with the elbow close to the body, with the thumb at the plastic marker, index, and middle fingers opposite [2]. If the above will be difficult, then any change in methodology will be allowed as per the faculty’s decision and will be documented from the video. The whole procedure will be videographed.

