#### Concealment mechanism {16b}

The random codes will be written on a piece of paper and put in opaque brown envelopes which will be sealed. Once a patient has been enrolled, the operating room’s technical staff will open an opaque, sealed envelope containing the group allocation and mark the ETT accordingly. Allocation concealment will be ensured, as the randomization code will not be released until the patient has been recruited into the trial, which takes place after all baseline measurements have been completed in the pre-anesthesia checkup, the evening before surgery.

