#### Implementation {16c}

Neither front-line care providers, investigators, nor participants will be aware of whether the next eligible participants will be receiving treatment or control intervention. One of the team members will enroll the participants and leave the set, sequentially numbered, generated by the research assistant, sealed opaque envelopes with the OT technician (OTT) responsible for anesthesia for the patient. The OTT will not be a part of the research team and will open the sealed envelopes to read the randomization sequence, which will be matched with the random number sequence generated earlier. He will be the one to mark the ETT at the designated site as per the number picked and the group it belongs to. The intubator will be asked to hold at the marked site after he/she confirms the optimal CL view. The assessors calculating time timings from the video will be blinded to the group the video belongs to.

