### Assignment of interventions: blinding

#### Who will be blinded {17a}

The patient, the outcome assessor, and the data analyst will be blinded to the study intervention.

The intraoperative anesthesia team will not be blinded to the study.

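### The CL >2 exclusion is judged after the tube has been marked, by a team that is not blinded and with no stated masking, so the allocation is knowable (though not shown to be known) at that moment

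*Protocol article*

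**What the plan says.** All references are to the Protocol article.

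- **Marking the tube.** Under Intervention description {11a}, Personnel, the technician "will select a sealed envelope after the patient enters the theater and the WHO checklist is completed. He will then mark the endotracheal tube", with a transparent sticker placed at 19 or 24 cm.
- **Grading the view.** Under Technique, laryngoscopy follows induction and at least 3 minutes of paralysis. When the trainee's call is that "the CL grade is optimal (CL < 3), it will be confirmed by the faculty or senior either verbally or visually". Only then "the tube will be handed over by the technician to the intubator". Implementation {16c} gives the same order for the grip: "The intubator will be asked to hold at the marked site after he/she confirms the optimal CL view".
- **Exclusion.** Eligibility criteria {10} lists among the exclusions "patients having Cormack Lehane (CL) grading more than 2 on direct laryngoscopy". Cases found to be CL >2 are filmed but left out of the analysis.
- **Blinding.** Section {17a} states: "The intraoperative anesthesia team will not be blinded to the study".
- **Concealment.** Section {16b} says that "the randomization code will not be released until the patient has been recruited into the trial", with baseline measurements completed the evening before surgery.
- **Analysis set.** Statistical methods {20a} refers to all randomized patients, and section {20c} plans both per-protocol and ITT analyses.

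**The concern.** One eligibility criterion is settled after randomization and after the allocation has been opened in the room. It is a subjective grade. Calling a borderline view 3 instead of 2 takes the patient out of the analysis. If the person grading has seen the mark, the call could depend on the arm, and the two analysed groups would then differ in airway difficulty for reasons other than chance.

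Three features of the protocol make this more than a formality:

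- Background {6a} records a belief, shared among peers, that holding farther from the tip is better. Recruitment {15} says that all 14 faculty and 31 residents know the protocol.
- The declared grade carries extra weight: under Position, a declared grade 1 or 2 makes the procedure adequate even when the table position is inexact.
- The blinded video assessors cannot be relied on to re-grade the view. A head-mounted camera is planned in only a few cases, and the protocol accepts that its axis differs from the intubator's.

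**Working it through.** **Order of events.** The protocol gives no figure for this point, so the first check is the sequence.

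1. Enrolment and baseline measurements, the evening before surgery ({16b}).
2. Patient in theatre, checklist done, envelope taken, tube marked (Personnel).
3. Induction and at least 3 minutes of paralysis (Technique).
4. Laryngoscopy; CL grade declared by the trainee and confirmed by faculty or a senior (Technique).
5. If the grade is below 3, the marked tube is handed over with the instruction to grip at the mark (Technique, {16c}).
6. If the grade is above 2, the case is filmed and excluded from the analysis ({10}).

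Allocation is opened at step 2 and the exclusion is decided at step 4. No section says that the mark or the opened envelope is kept from the trainee or faculty between these steps. The argument in {16b} covers step 1, and CL grade cannot be among the measurements made then.

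**Possible size.** The protocol gives no CL >2 rate and no times for such cases, so everything below except the pilot mean, the pilot SD and the targets is an assumption.

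Inputs from Sample size {14}: mean m = 8.83 s; SD 4.07 s; target difference 1 s, also stated as 20%, and 0.20 × 8.83 = 1.77 s.

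*Version A.* Both arms have the same true mean m. A fraction q is excluded, and the excluded cases average R times m. The mean of those kept is m(1 − qR)/(1 − q).

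| R | 5% excluded | 7% excluded | 10% excluded | Shift, 5% v 7% | Shift, 5% v 10% |
|---|---|---|---|---|---|
| 1.5 | 8.60 s | 8.50 s | 8.34 s | 0.10 s | 0.26 s |
| 2 | 8.37 s | 8.17 s | 7.85 s | 0.20 s | 0.52 s |

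For example, with R = 2 and q = 0.10: 8.83 × (1 − 0.20)/0.90 = 7.85 s.

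*Version B.* Excluded cases are 10 s slower than those kept. The shift is 10 s times the difference in exclusion rates: 0.03 × 10 = 0.3 s and 0.05 × 10 = 0.5 s. The 10 s excess is a high assumption: 10/4.07 = 2.5 pilot SDs.

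The two versions together span roughly 0.1 to 0.5 s. That is 10 to 50% of the 1 s target, or about 6 to 28% of 1.77 s (0.1/1.77 and 0.5/1.77). If both arms exclude the same fraction of comparable cases, the shift is zero. The arm that excludes more slow cases looks faster.

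**The case against.** The strongest reply is that the design already separates grading from allocation. A technician outside the research team opens the envelope and marks the tube. The mark is a transparent sticker. Both the handover and the grip instruction come after the view is declared. This stands as a real reduction of risk. It is not removal, because the marked tube is in the room before the grade is called and nothing says that it is covered.

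A second reply is that this argues from silence in a condensed article, and that how a technician holds a tube may be described elsewhere. That is fair, and it is why the point is put as knowable and not as known. A reader might take the {17a} statement as proof that the graders know the arm. It is not. A team told to grip at a visible mark cannot be blinded during the intervention, and the statement may mean no more than that.

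A reader might also infer that allocation concealment fails and that {16b} is wrong. The documents do not support this: what {16b} says about release of the code holds for enrolment. The issue is exclusion after randomization.

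Finally, an ITT analysis that keeps CL >2 cases would limit the bias. That is correct, but {10} says that these cases are left out of the analysis, so the remedy cannot be counted on until the sections agree.

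**Conclusion.** The concern holds as an open route to differential exclusion after randomization, not as a demonstrated bias. The documents establish the order of steps, the subjective grade, the unblinded team and the exclusion from analysis. They do not establish that anyone grading sees the mark, or that either site would prompt more grade 3 calls, so size and direction are both unknown. A reader might conclude that harder airways are being removed selectively from one arm, or that half of the target effect is at risk. The first has no support in the documents, and the second is only the top of an assumed range.

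The 0.1 to 0.5 s range rests on assumed exclusion differences of 2 to 5 percentage points, on assumed times for the excluded cases, and on the pilot mean applying to trainees. The point still merits action, because the upper end is not negligible against either stated target and closing the gap costs very little.

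**What to change.** 1. Have the technician open the envelope and mark the tube out of the team's view, and keep the tube covered until the CL grade has been declared and confirmed aloud on the existing video recording. Enter the grade on the case record form afterwards, so that no pause is added during laryngoscopy. The grade precedes the grip, so an exclusion made without knowledge of the arm does not bias the comparison.
2. Report the number of CL >2 exclusions by arm, including for patients already enrolled. Masking protects only patients still to be recruited; for the others, the count by arm is the available check.
3. Reconcile Eligibility criteria {10}, which leaves CL >2 cases out of the analysis, with sections {20a} and {20c}, which refer to all randomized patients and plan an ITT analysis. Report an analysis that retains CL >2 cases alongside the one that excludes them. These procedures are filmed in any case; the plan needs to state how their time to intubation is taken.

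The cost is a short change to the technician's instructions, one line in the participant flow and one additional analysis. No staff or equipment is added beyond a cover for the tube, and clinical management is unchanged.

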##### Position

The head position will be optimized to get the best possible view of the vocal cords. The “sniffing position” that aligns the oral, pharyngeal, and laryngeal axes will be achieved by elevating the patient’s head, extending the head at the neck, and aligning the ears horizontally with the sternal notch. In morbidly obese patients, rolls will be utilized [2]. The operating table’s position will be at the height of the intubator’s xiphoid process and her/his eyes about 1 foot (∼30 cm) above the patient’s face to provide proper angles and distances for laryngoscopy [5]. If the table position is not “exact” (in the videography), but the intubator has declared a CL grade 1 or 2 view, the procedure will be considered adequate as the head and neck position has been considered less critical for a successful LEI [4].

##### Laryngoscope

All procedures will be performed with a curved blade Macintosh laryngoscope, size ¾ as appropriate for the patient.

##### Endotracheal tube

All patients will be intubated with new, single-use, room temperature, PVC, high-volume, low-pressure, cuffed ET of appropriate size. All tubes are procured from the same company at the institute. The use of a stylet or bougie will not be allowed in the first attempt.

##### Medications

All the patients in both groups will undergo a standard anesthesia technique using Fentanyl 2 mcg per kg for analgesia, 2.5 mg per kg of propofol for induction, and 0.07–0.1 mg/kg of vecuronium for muscle relaxation. Maintenance of anesthesia will be with isoflurane or sevoflurane, aiming for an agent-appropriate MAC intubation.

#### Technique

After induction and a minimum of 3 min of administering the paralytic agent, the intubator will perform the laryngoscopy. Once the intubator declares that the CL grade is optimal (CL < 3), it will be confirmed by the faculty or senior either verbally or visually. Once declared as an “optimum laryngoscopic view,” the tube will be handed over by the technician to the intubator and prior instruction will be given to take the first attempt at the marked point, with the elbow close to the body, with the thumb at the plastic marker, index, and middle fingers opposite [2]. If the above will be difficult, then any change in methodology will be allowed as per the faculty’s decision and will be documented from the video. The whole procedure will be videographed.

#### Post-procedure

Post-extubation, the airway will be checked for any complications like bleeding or sore throat in the immediate postoperative period. If there is an event of failed intubation by the trainee, then the senior will be assessed during the process of intubation.

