### Criteria for discontinuing or modifying allocated interventions {11b}

If the intubator cannot intubate at the given tube mark, he will be allowed to change the site of grip—the site change will be noted from the video. If he/she still fails, the consultant can take over.

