### Methods in analysis to handle protocol non-adherence and any statistical methods to handle missing data {20c}

Sensitivity analysis will be done to handle the missing data. Missing data will be handled with multiple imputations. Per-protocol and ITT analyses will both be done.

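### Trainee failure, take-over and grip change are excluded after randomization in one place, permitted or assessed in others, and promised to an ITT analysis with no stated value

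*Protocol article*

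**What the plan says.** Six sections of the protocol article bear on a patient whose trainee does not intubate at the marked point.

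- **Technique:** the view is confirmed as adequate before the tube is handed over. Then "prior instruction will be given to take the first attempt at the marked point". If that proves difficult, "any change in methodology will be allowed as per the faculty’s decision and will be documented from the video".
- **Section {11b}, on stopping or changing the allocated intervention:** "If the intubator cannot intubate at the given tube mark, he will be allowed to change the site of grip". After that, "If he/she still fails, the consultant can take over".
- **Post-procedure:** "If there is an event of failed intubation by the trainee, then the senior will be assessed during the process of intubation".
- **Eligibility criteria {10}, item iii:** procedures with deviation from the method, airway adjuncts "or take-over by the consultant (unanticipated difficult airway), will be video recorded but excluded from the analysis". **Dropout criteria** likewise drop any change of grip once the tube is held.
- **Statistical methods {20a}:** all randomized patients are to be analysed.
- **Section {20c}:** "Per-protocol and ITT analyses will both be done". Neither analysis is named as primary, and missing data are to be multiply imputed.

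Outcomes {12} runs TTI from holding the tube to removing the laryngoscope, once a tube has been declared passed under vision. Neither that section nor the timeline table, which lists one start time and one stop time, names the attempt or the operator.

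**The concern.** The trial asks how the place of grip affects intubation by trainees. A trainee who fails at the allocated mark, changes grip or is replaced has had the worst result that the allocation can produce. The protocol deals with these patients in incompatible ways: removed from the analysis, assessed through another operator, and kept as randomized.

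The exclusions follow randomization and, for grip change and take-over once the tube is held, may depend on the allocated grip. The analysed groups are then no longer those that randomization formed, and the arm that causes more failures loses more of its slow cases. An ITT analysis would normally guard against this. Here it has no stated value for a failed case, and the two sources in sight, imputation and the senior's performance, both tend to supply a time typical of success. At stake are the direction and size of the primary comparison, and the first-pass success rate.

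**Working it through.** **Step 1: follow one patient through the text.** The trainee has a confirmed good view, takes the tube at the mark, fails, changes grip, fails again, and the consultant takes over.

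- {11b} allows both events.
- Dropout criteria remove the patient for the grip change, and Eligibility criteria {10} remove the patient for the take-over.
- Post-procedure has the senior assessed.
- {20a} and {20c} keep the patient in the all-randomized and ITT analyses.
- Outcomes {12} scores attempts, additional operators and alternative techniques in the IDS, so outcome recording expects such patients.

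The stated reason for the exclusions is to stop poor laryngeal views confounding TTI. That does not cover this patient, whose view was confirmed before the tube was handed over.

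**Step 2: which value could the patient receive?**

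1. None (excluded): the arm mean is the mean of its successes.
2. Imputed: values drawn from observed successes resemble successes.
3. The senior's time, if Post-procedure is read that way: an expert's time.
4. The trainee's own result, counted as a failure: not provided for.

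If failed cases would have taken longer than successes, routes 1 to 3 all flatter the arm with more failures.

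**Step 3: illustration of direction.** The plan contains no figure for this to reproduce. From Sample size {14} come the pilot mean of 8.83 s and the two stated targets, 1 s and 20% (0.20 × 8.83 = 1.77 s). Everything else is assumed: successes average 8.83 s in both arms, failure rates are 5% in one arm and 10 to 20% in the other, and a failed case truly lasts 20 to 40 s.

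True mean difference = (difference in failure rate) × (failed time − 8.83):

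- 0.05 × (20 − 8.83) = 0.56 s
- 0.05 × (30 − 8.83) = 1.06 s
- 0.15 × (40 − 8.83) = 4.68 s

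What the analysis would show instead:

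- Failures excluded, or imputed with the mean of successes: 8.83 − 8.83 = 0 s.
- Senior's time used, at 8.83 s: 0 s.
- Senior's time used, at an assumed 6 s: 0.05 × (6 − 8.83) = −0.14 s to 0.15 × (6 − 8.83) = −0.42 s. The failing arm would look slightly faster.

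**Step 4: first-pass success.** As an extreme case, suppose true rates of 95% and 90%, with every failure ending in an excluded event. After exclusion both arms show 100%, and a 5-point difference disappears. Trainees who fail first but succeed later without an excluded event would stay in, so the real distortion would be smaller.

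**The case against.** The strongest reply is that the protocol never says the senior's time becomes the patient's TTI. Post-procedure says only that the senior is assessed, and the exclusions keep take-over and changed-grip cases out of the final analysis. {20c} also offers multiple imputation as another source of a value. All of that stands. A reader might infer that expert times will be entered for failures and make a failing arm look fast. The text permits that reading in the ITT set but does not state it.

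A reader might also infer that the clock restarts at a second hold of the tube, at a grip no longer tied to the mark. With one start and one stop time listed, the plainer reading is first hold to final removal, under which a failed pass or a regrip lengthens TTI. Nor is reversal of the comparison supported. It appears above only with an assumed 6 s senior, and then by less than the 1 s target.

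Two further replies are partly right. First-pass success, the IDS and noted changes of grip do make failure visible, but only in an analysis that keeps these patients. Attempt-level timing rules are commonly left to a full protocol or SAP, and their absence from an article is not the finding. The finding is that statements the article does make contradict one another.

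**Conclusion.** The point holds as a contradiction between the post-randomization exclusions ({10} and Dropout criteria), the permitted events ({11b}), the unexplained assessment of the senior (Post-procedure) and the promised all-randomized and ITT analyses ({20a}, {20c}). Exclusion or imputation from successes would pull TTI in favour of the arm with more trainee failures. So would the senior's time, if it were used. Exclusion would also distort first-pass success.

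The direction rests on two assumptions: failure depends at least partly on the allocated grip, and failed cases would have taken longer than successful ones. The size cannot be derived from the documents. The 0.6 to 4.7 s range is an illustration under assumed rates and times. It shows only that the effect could be of the same order as the 1 s and 1.77 s targets. If failures are rare, or equally frequent in both arms, the bias in the difference is small.

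**What to change.** Reconcile the six sections for the analysis only, leaving the clinical rules on grip change and take-over as they are.

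- Keep every randomized patient in the ITT analysis, and confine the exclusions in Eligibility criteria {10} item iii and in Dropout criteria to the per-protocol analysis.
- State that only the allocated trainee's performance supplies endpoints, with TTI running from the first hold of the tube.
- Count trainee failure or take-over as first-pass failure and as the least favourable TTI outcome in a rank-based test. Do not treat it as missing data to be imputed. The Mann-Whitney test is already foreseen in {20a}.
- State in Post-procedure that the senior's time is descriptive and never the patient's TTI.

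The cost is wording: procedures are already video recorded, including those now excluded. The drawback is a longer TTI tail in the ITT set, so that result would be summarised by ranks or medians rather than as a mean difference in seconds.
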